## **9 Test Patients**

Up to six test patients will be recruited to assess the engineering performance of automated single-hormone CLS in regulating glucose levels in free-living inpatient conditions. Participants will stay at the Centre for Innovative Medicine at McGill University Health Centre Research Institute or at Institut de recherches cliniques de Montréal under the supervision of a nurse or a research staff with an MD on site or on call. No admission visits is required (data obtained from usual medical file), but may be conducted, for these patients. Participants will be admitted at the clinical research facility between 7:30 am and 11:00 am and will stay at the research facility for 24 hours. A glucose sensor will be inserted by the participant. Participants will be trained on the closed-loop system, and that includes training on connection and disconnection of the system and meal boluses (a user guide will also be given to participants). Participants will have the freedom to choose their day schedule. Participants will freely choose their meals from a large choice of pre-prepared frozen meals. Fresh fruits and vegetables, cheese, yogurt, beverages and bread will also be available at any time. Applicable endpoints detailed in Section 8 will be

calculated after the all test patients have completed the in-patient intervention. The data of the test patients will not be used in the statistical analysis of the main trial.

## **10 Monitoring Plan**

A research assistant at IRCM not implicated in this research project will be in charge of monitoring data.

A first monitoring will be done after the first participant completes the study. Afterwards, monitoring will occur after each five patients complete the study.

The monitoring plan includes verifying that:

- The study is conducted according to the study protocol as well as according to Good Clinical Practice guidelines and local regulation;
- Protocol deviations have been documented and reported to the research ethics board;
- Study devices are being used according to the study protocol;
- Signed and dated informed consent forms have been obtained from each participant at the point of enrollment or before any study procedures are undertaken;
- Case report forms and other study documents are accurate, complete, up to date, stored and maintained appropriately;
- Appropriate corrections, additions or deletions are made to case report forms, dated, explained if necessary and initiated by the person who did the corrections, additions or deletions;
- All serious adverse events and device deficiencies have been reported to the research ethics board;
- All other documents related to the study and correspondence are maintained in the study binder;
- Participant's withdrawal has been documented.

All monitoring activities will be documented in a written report kept in the study binder. This report will include:

- The date of the monitoring visit;
- The name of the monitor;
- A summary of what the monitor reviewed;
- Significant findings and protocol deviations.

A Data Safety Monitoring Board will be composed of 3 researchers in the field of diabetes and with knowledge about CLS. The role of the Data Safety Monitoring Board will be to periodically review and evaluate the study data for participant safety, study conduct and progress, and to make recommendations concerning the continuation, modification, or termination of the trial. The first DSMB meeting will be planned after the first three patients complete the study. Additional DSMB meeting will be planned in the case of an SAE (e.g. severe hypoglycemia) to ensure rapid revision (within less than 1 week) and provide advice to the clinical team.

## **11 Adverse events, Adverse device effects and Device deficiencies**

### **11.1 Definitions**

Adverse event (AE): any untoward medical occurrence, unintended disease or injury, or untoward clinical signs in participants whether or not related to the study devices.

Adverse device effect (ADE): adverse event related to the use of a study device. This definition includes adverse events resulting from insufficient or inadequate instructions for use, or any malfunction of the study device. This definition also includes any event resulting from use error or from intentional misuse of the study device.

Device deficiency: inadequacy of the study device with respect to its reliability, safety or performance.

Serious adverse event (SAE): adverse event that a) led to death; b) led to serious deterioration in the health of the subject, that either resulted in 1) a life-threatening illness or injury, or 2) a persistent or significant disability/incapacity, or 3) in-patient or prolonged hospitalization, or 4)

medical or surgical intervention to prevent life-threatening illness or injury or persistent or significant disability/incapacity.

Serious adverse device effect (SADE): adverse device effect that has resulted in any of the consequences characteristic of a serious adverse event.

Unanticipated serious adverse device effect (USADE): serious adverse device effect which by its nature, incidence, severity or outcome has not been identified in the current version of the risk analysis report.

## 11.2 Responsibilities of the Principal Investigator

The principal investigator is responsible for:

- The classification of AE and evaluation of their seriousness and relationship to the study device.
- Reviewing all device deficiencies and determine and document in writing whether they could have led to a SADE.
- Reporting to the research ethics board all SAE and device deficiencies within 30 days of becoming aware of the problem.
- Reporting to the research ethics board and regulatory authorities all SAE, SADE and USADE within 10 days of becoming aware of the problem.
- Reporting all relevant safety information to the Data Safety Monitoring Board.
- Ensuring that the research ethics board and the regulatory authorities are informed of significant new information about the study, and in case of SADE and device deficiencies that could have led to SADE, determine whether the risk analysis needs to be updated and assess whether corrective or preventive action is required.

## 11.3 Reporting of SAE, SADE and USADE

When reporting an SAE, SADE or USADE, the following information will be presented:

- Intensity: the intensity of an adverse event can be classified as mild, moderate or severe.
  - **Mild:** no or transient symptoms, no interference with the subject's daily activities.
  - **Moderate:** marked symptoms, moderate interference with the subject's daily activities.

- **Severe:** considerable interference with the subject's daily activities; unacceptable.
- Relationship to study procedures/devices: based on the principal investigator's judgement, the relationship to study procedures/devices can be probable, possible or unlikely.
  - **Probable:** good reason and sufficient documentation to assume a causal relationship.
  - **Possible:** a causal relationship is conceivable and cannot be dismissed.
  - **Unlikely:** the event is most likely related to aetiology other than the trial product.
- Final outcome:
  - Recovered/resolved: the participant has fully recovered.
  - Recovering/resolving: the condition is improving and the participant is expected to recover from the event.
  - Recovered/resolved with sequel: the participant has recovered from the condition, but with lasting effect due to a disease, injury, treatment or procedure.
  - Not recovered/not resolved: the condition of the participant has not improved and the symptoms are unchanged.
  - Fatal: this term is only applicable if the participant died from a condition related to the reported AE.
  - Unknown: this term is only applicable if it is not possible to follow up with the participant.

## 11.4 Reporting Device Deficiencies

When reporting a device deficiency, the following information will be presented:

- Description of the deficiency as well as the circumstances in which the deficiency happened.
- Measures to correct the deficiency.
- Report if the deficiency induced an adverse event.

## 12 Suspension or Premature Termination of the Study

The principal investigator, the REB, the DSMB or Health Canada may decide to suspend or stop the trial at any time.

If a trial is suspended or prematurely terminated, the principal investigator must inform the participants as well as the REB and Health Canada and provide a detailed written explanation.

If in the course of the study, the benefit-risk analysis changes, the new evaluation must be provided to the REB and Health Canada.

If the study is suspended, it can then only be resumed after obtaining a new written approval by REB and Health Canada.

## **12.1 Suspension of the study**

The study can be suspended by the DSMB based on data or SAE review.

## **12.2 Premature termination of the study**

The study will be prematurely ended 1) if the DSMB establish that the risk-to-benefit ratio of the trial is not acceptable, 2) if three or more patients encounter an SAE related to the study devices with single-hormone CLS or 3) if a death occurs with single-hormone CLS and it is established that the cause of death is related to the CLS.

# **13 Ethical and Legal Consideration**

## **13.1 Good Clinical Practice**

This study is to be conducted according to globally accepted standards of good clinical practice (as defined in the ICH E6 Guideline for Good Clinical Practice, 1 May 1996), in agreement with the Declaration of Helsinki and in keeping with local regulations.

## **13.2 Delegation of Investigators Duties**

The investigator should ensure that all persons assisting with the trial are adequately qualified, informed about the protocol, any amendments to the protocol, the study treatments, and their trial-related duties and functions.

The investigator should maintain a list of sub-investigators and other appropriately qualified persons to whom he or she has delegated significant trial-related duties.

### **13.3 Participant Information and Informed Consent:**

After reading the relevant documents, the participant must give consent in writing. This consent must be confirmed by the personally dated signature of the participant and by the personally dated signature of the person conducting the informed consent discussions.

A copy of the signed consent documents must be given to the participant. The original signed consent documents will be retained by the investigator.

The investigator will not undertake any measures specifically required only for the clinical study until valid consent has been obtained.

It is suggested that the investigator inform the participant's primary physician about the participant's participation in the trial, if the participant has a primary physician other than the study investigator.

### **13.4 Confidentiality**

Participant names will be kept in strictest confidence. Participants will be identified by their participant identification numbers which does not contain date of birth or initials. Study data stored on a computer will be stored in accordance with local data protection laws.

The investigator will maintain a personal participant identification list (participant numbers with the corresponding participant names) to enable records to be identified. Participants' identifiers and contact details will be stored locally under strict security.

### **13.5 Approval of the Clinical Study Protocol and Amendments**

Before the start of the study, the clinical study protocol, informed consent document, and any other appropriate documents will be submitted to the IEC/IRB with a cover letter or a form listing the documents submitted, their dates of issue, and the site for which approval is sought.

Before the first participant is enrolled in the study, formal written approval from the IEC/IRB must be obtained and all ethical and legal requirements must be met.

The IEC/IRB must be informed of all subsequent protocol amendments and administrative changes, in accordance with local legal requirements.

The investigator must keep a record of all communication with the IEC/IRB.

### 13.6 Record Retention

All study records must be kept according to ICH guidelines.

## 14 Publication Policy

The principal investigator commits to communicating, and otherwise making available for public disclosure, results of this study. Public disclosure includes publication of a paper in a scientific journal, abstract submission with a poster or oral presentation at a scientific meeting, or disclosure by other means. No confidential information will be disclosed.

## **Annex A. Ketone Management Procedure**

Participants will be asked to measure their capillary ketones when blood glucose levels are above **16 mmol/L for a period longer than an hour** and/or when they experience symptoms of hyperglycemia (increased urination, significant thirst, fatigue, blurred vision, stomach aches, headaches, nausea, vomiting ...).

**If blood ketones levels are:**

**Between 0.0 and 0.6 mmol/L**, instruct participant to:

- Drink sugar-free and caffeine-free fluids.
- Check the cartridge, catheter and insertion site.
- Avoid skipping meal and have a minimal amount of carbohydrate (> 30g) in such meal.
- Use the iMAP or participant personal insulin pump to calculate a correction bolus. Administer correction bolus via the pump.
- Monitor signs and symptoms of hyperglycemia (excessive thirst, urination, abdominal pain, nausea, weakness, etc...) and ketones.
- Monitor blood glucose and ketone levels 2 hours after correction bolus is administered.
- If hyperglycemia persists (> 16 mmol/L) and/or blood ketone levels increase 2 hours post correction, change infusion set and follow ketone management procedure.

**Between 0.6 and 1.5 mmol/L**, instruct participant to:

- Contact their study nurse
- Drink sugar-free and caffeine-free fluids (aim 200-250 ml every 30-60 minutes)
- Use bolus calculator on insulin pump or iMAP to calculate correction bolus. Administer the bolus via syringe or insulin pen. (If on CLS, the participant should disconnect the study pump from their body and deliver the same bolus through the system, so it accounts for the insulin given via the syringe, and proper IOB is calculated)

*\*Participant should be encouraged to eat a small amount of carbs (15-45g), there should be a bolus administered for any carb intake.*

- Change the pump cartridge, tubing and infusion set.
- Verify if cannula seems kinked or blocked, and if there is blood at the old insertion site. Check if their insulin was properly stored (as per supplier recommendations). This information should be charted in participant file by the study nurse.
- Monitor signs and symptoms of hyperglycemia (excessive thirst, urination, abdominal pain, nausea, weakness, etc...) and ketones
- Monitor blood glucose and blood ketones levels 2 hours after correction bolus is administered
- If hyperglycemia persists or blood ketone levels remain positive (one or both values have not decreased from initial values), notify study physician and keep supporting participant by following the ketone management procedure.

**Above 1.5 mmol/L**, instruct participant to:

- Contact their study nurse (study physician should be notified immediately for ketone values above 3.0 mmol/L).
- Drink sugar-free and caffeine-free fluids (aim at 200-250 ml every 30-60 minutes)
- Use bolus calculator on insulin pump or iMAP to calculate correction bolus. Multiply **correction bolus** by 1.5. (Ex correction bolus recommendation = 2U, Multiply by 1.5 = 3U). Administer the bolus via syringe or insulin pen. If on CLS, the participant should disconnect the study pump from their body and deliver the same bolus through the system, so it accounts for the insulin given via the syringe, and proper IOB (insulin on board) is calculated.
- *\*Participant should be encouraged to eat a small amount of carbs (15-45g), there should be a bolus administered for any carb intake. It's important that only the correction part of the bolus is multiplied.*
- Change the cartridge, tubing and infusion set.
- Verify if cannula seems kinked or blocked, and if there is blood at the old insertion site. Check if their insulin was properly stored (as per supplier recommendations). This information should be charted in participant file by the study nurse.

- Monitor signs and symptoms of hyperglycemia (excessive thirst, urination, abdominal pain, nausea, weakness, etc...) and ketones
- Monitor blood glucose and blood ketones levels 2 hours after correction bolus is administered
- If hyperglycemia persists or blood ketone levels remain positive (one or both values have not decreased from initial values), notify study physician and keep supporting participant by following the ketone management procedure.

In the event of positive blood ketones (above 0,6 mmol/L), the participant will only return to pump or iMAP pump therapy once ketones are below 0,6 mmol/L.

Participants will record all blood ketone levels measured and infusion set changes in the Study Participant Journal. The reasons for infusion set changes are documented in the journal (ex: planned vs unplanned).

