For both interventions, participants will be asked to record hypoglycemia episodes, calibrations, catheter and sensor changes and hyperglycemic episodes with ketones in a diary provided to them. After each intervention, participants will be asked to complete the diabetes treatment satisfaction questionnaire. This questionnaire will be used to evaluate the impact of, and the satisfaction with study devices.

The first intervention visit will be maximum 30 days after the run-in period. Intervention visits should be separated by 4-40 days. We will have 24-hour technical support available during all interventions.

The duration of each intervention will be 12 days.

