#### **8.1.2 Secondary endpoints**

1. Percentage of time of glucose levels spent *a.* between 3.9 and 7.8 mmol/L; *b.* below 3.9 mmol/L; *c.* below 3.3 mmol/L; *d.* below 2.8 mmol/L; *e.* above 10.0 mmol/L; *f.* above 13.9 mmol/L; *g.* above 16.7 mmol/L.
2. Percentage of time (00:00-6:00) of glucose levels spent *a.* below 3.9 mmol/L; *b.* between 3.9 and 7.8 mmol/L; *c.* between 3.9 and 10.0 mmol/L; *d.* below 3.3 mmol/L; *e.* below 2.8 mmol/L; *f.* above 10.0 mmol/L; *g.* above 13.9 mmol/L; *h.* above 16.7 mmol/L.

3. Mean glucose levels.
4. Fasting sensor glucose levels.
5. Standard deviation of glucose levels and insulin delivery.
6. Coefficient of variance of glucose levels and insulin delivery.
7. Between-day variability in glucose levels and insulin delivery.
8. Total insulin delivery.
9. Number of hypoglycemic events less than 3.1 mmol/L (>20 minutes).
10. Number of nights with hypoglycemic events less than 3.1 mmol/L (>20 minutes).
11. Number of days with hypoglycemic events less than 3.1 mmol/L (>20 minutes).
12. Total number of hours and percentage of time of sensor availability.
13. Time (hours) between failures due to sensor unavailability.
14. Time (hours) between failures due to pump connectivity.
15. Number of days with at least one technical problem.
16. Number of hours and percentage of time when patients switched back to sensor-augmented pump therapy.
17. Number of hours and percentage of time when the CLS was automatically switched to sensor-augmented pump therapy.
18. Number of calls and patients calling for technical issues related to CLS.

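### Insulin injected during a ketone episode enters the pump record on CLS only, and no recording list asks for the dose, so insulin endpoints taken from pump records would count it in one arm and miss it in the other

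*Protocol*

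**What the plan says.** Annex A of the protocol covers both interventions. In its two upper ketone bands (0.6 to 1.5 mmol/L, and above 1.5 mmol/L) the correction bolus is calculated on the pump or the study system but given outside it: "Administer the bolus via syringe or insulin pen". For closed-loop participants there is a further step: "If on CLS, the participant should disconnect the study pump from their body and deliver the same bolus through the system". The stated reason is "so it accounts for the insulin given via the syringe, and proper IOB (insulin on board) is calculated". Nothing equivalent is asked of SAPT participants, who use their own pump (Section 7.2.2). In either arm, after a positive ketone reading, "the participant will only return to pump or iMAP pump therapy once ketones are below 0,6 mmol/L".

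Three places say what participants write down:

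- Annex A: "Participants will record all blood ketone levels measured and infusion set changes in the Study Participant Journal", with the reason for each set change.
- Section 7.2.2, both interventions: "record hypoglycemia episodes, calibrations, catheter and sensor changes and hyperglycemic episodes with ketones in a diary".
- Section 2: a journal of low and high glucose episodes and of catheter and reservoir changes.

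None names an injected insulin dose. Annex A also says what the nurse charts (state of the cannula, blood at the old site, insulin storage), and its Reporting part makes every ketone event above 0.6 mmol/L an adverse event in the chart. Neither mentions units injected.

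Section 8.1.2 lists "Total insulin delivery" as endpoint 8. Endpoints 5, 6 and 7 include the standard deviation, coefficient of variation and between-day variability of insulin delivery. No data source is given for any of them.

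**The concern.** Pump records are the obvious source for insulin delivery. With that source, one and the same treatment would leave different traces in the two arms: the injected units appear in the closed-loop log because the participant re-enters them, and do not appear in the log of the participant's own pump. In a crossover, that difference goes straight into the within-person contrast for anyone affected.

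This is a data-capture matter. A statistical analysis plan can rule that injected insulin counts, but it cannot supply a dose that nobody was asked to write down. At stake are the comparisons of total insulin and its variability, which help a reader judge whether a gain in time in range came with more or less insulin.

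**Working it through.** The plan gives no figure for any insulin endpoint, so there is none to reproduce. Its sample size of 36 (Section 8.2) concerns time in range and is not affected.

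**Step 1. Follow one injected bolus through the recording rules.**

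- Given by syringe or pen: CLS yes, SAPT yes (Annex A).
- Repeated through the disconnected pump: CLS yes, SAPT not asked (Annex A).
- Units listed for the journal or diary: no in both arms (Section 2, Section 7.2.2, Annex A).
- Units required in the nurse's charting or the adverse event entry: no in both arms (Annex A).
- Episode itself identifiable: yes in both arms (diary, nurse contact, adverse event).

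As written, the dose is captured by rule in one arm only.

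**Step 2. Size for an affected participant, if only pump records are used.**

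Inputs: 3 U from the Annex's worked example ("Ex correction bolus recommendation = 2U, Multiply by 1.5 = 3U"); 12 days per intervention (Section 7.2.2); total daily dose of 30-60 U, which is an assumption.

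- Share of that day = 3 / daily dose: 3/60 = 5% to 3/30 = 10%.
- Share of the period = 3 / (12 x daily dose): 3/720 = 0.42% to 3/360 = 0.83%.
- Average per day = 3/12 = 0.25 U.

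The Annex also encourages 15-45 g of carbohydrate with a bolus. If that bolus is injected too, at an assumed 1 U per 10 g, the dose becomes 3 + 1.5 = 4.5 U to 3 + 4.5 = 7.5 U. That is 4.5/60 = 7.5% to 7.5/30 = 25% of the day, and 4.5/720 = 0.6% to 7.5/360 = 2.1% of the period. At an assumed 20 U per episode, the share of the period is 20/720 = 2.8% to 20/360 = 5.6%.

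**Step 3. Size for the arm mean.**

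Shift = (fraction of participants with one episode) x (units missed) / 12. The fraction is not in the protocol; 5-40% is assumed.

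- 3 U: 0.05 x 0.25 = 0.01 U/day to 0.40 x 0.25 = 0.10 U/day.
- 20 U: 0.05 x 20/12 = 0.08 U/day to 0.40 x 20/12 = 0.67 U/day.

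**Step 4. Effect on day-to-day variability.**

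Take the variance of n = 12 daily totals. If a dose b is missing on a day whose true total lies d above the participant's mean, the variance changes by -2bd/(n-1) + b²/n. With b = 3 this is -6d/11 + 0.75 (U squared), which is zero at d = 0.75 x 11/6 = 1.4 U. The omission lowers the recorded variance if the true total that day is more than 1.4 U above the mean, and raises it otherwise. No percentage can be given, because the protocol states no day-to-day SD and does not define the between-day measure. But these measures depend on single-day deviations, and there the missing dose is 5-10% of a day, against 0.4-0.8% of the total.

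**The case against.** The strongest reply is that the harm depends on a premise the protocol does not state. Section 8.1.2 gives no source for insulin delivery, and derivation rules for secondary endpoints are commonly left to an analysis plan, which is not at hand. The closed-loop re-entry is there so that the algorithm knows the insulin on board; it is not an endpoint recording rule. Each episode is flagged in both arms by the diary, a call to the nurse and an adverse event entry, any of which may in practice hold the dose. The effect is small and confined to secondary endpoints that carry no power calculation.

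Most of this stands and limits the point. It does not remove it: none of those records is required to hold the units, and a later rule on sources cannot recover them.

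A reader might infer more than the text supports:

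- *That the insulin endpoints do measure different quantities in the two arms.* This follows only if they come from pump records alone.
- *That the error always runs in one direction.* That holds for the effect of the missing bolus on the SAPT total. It does not hold for the variability measures (Step 4) or for pump-record error as a whole: the Annex does not say how basal insulin logged while disconnected is treated, and a log may count insulin that a blocked cannula never delivered, in either arm.
- *That an episode means three injections, or 9 U* (15-30% of a day, 1.25-2.5% of the period at 30-60 U/day). The Annex asks for glucose and ketones to be checked two hours after the bolus and for the procedure to be followed further; it does not state a repeat injection every two hours.

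**Conclusion.** The point holds in conditional form. Annex A creates an entry for the injected bolus on CLS and none on SAPT, and no recording list in the protocol asks for the dose. If endpoints 5 to 8 are computed from pump records, that insulin is counted in one arm and missed in the other.

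The likely effect on arm means is small: 0.01-0.10 U/day for one 3 U dose in 5-40% of participants, and at most 0.67 U/day at 20 U. The variability measures of an affected participant could be hit harder, in a direction that cannot be fixed in advance. The daily dose, the episode frequency and the 20 U figure are assumptions; only the 3 U and the 12 days come from the protocol. The primary endpoint, which is sensor-based, and the sample size are unaffected. This is a worthwhile improvement to data capture and does not threaten the trial's main conclusion.

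**What to change.** - Add an entry to the participant journal, used in both periods, for the time and units of every insulin dose given by syringe or pen.
- State the data source for endpoints 5 to 8.
- Compute these endpoints on pump plus injected insulin, counting each injected dose once: add it to the pump total on SAPT, and do not add it again on CLS where the pump record already holds the re-entered bolus.

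The cost is one journal line, one data step and a small extra burden for participants who have a ketone episode. The journal line has to be in place before the data are collected. The change concerns recording and derivation only and implies no change to ketone management.

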## Reporting

All positive blood ketones events ( $> 0.6$  mmol/L) will be documented as Adverse Events (AE) in the participant chart. Should the local ERB require submission for this type of event, AE will be submitted to ERB for review. Should the AE be classified as serious by study physician (hospitalization required, etc...), the event will be documented as SAE and will be reported to ERB, DSMB and regulatory authorities.

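### Annex A's 2-hour physician-notification sentence, in the two upper ketone bands, names one trigger (values still raised) and explains it as another (values not falling), and the two can give opposite instructions

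*Protocol*

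**What the plan says.** Annex A sorts ketone readings into three bands. In the middle and top bands the participant contacts the study nurse, takes a correction bolus, and is then re-checked: "Monitor blood glucose and blood ketones levels 2 hours after correction bolus is administered". Both bands then carry the same sentence: "If hyperglycemia persists or blood ketone levels remain positive (one or both values have not decreased from initial values), notify study physician".

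The annex uses *positive* as a level in two other places:
- Return to pump therapy, at the end of the band instructions: "In the event of positive blood ketones (above 0,6 mmol/L), the participant will only return to pump or iMAP pump therapy".
- The Reporting section, on which events are documented as adverse events: "All positive blood ketones events ( $> 0.6$ mmol/L".

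The lowest band has its own 2-hour rule: "If hyperglycemia persists (> 16 mmol/L) and/or blood ketone levels increase 2 hours post correction". It gives persisting hyperglycemia as a level and ketones as a trend, and the action is an infusion-set change, not a call to the physician.

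One further notification rule stands in the top band: "study physician should be notified immediately for ketone values above 3.0 mmol/L".

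**The concern.** The main words of the 2-hour sentence describe a state, namely glucose still high or ketones still positive. The bracket describes a direction, namely one or both values failing to fall. A reading can be lower than at the start and still be high, so the two are not equivalent.

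The sentence decides whether the study physician hears, at two hours, about a ketone episode that is improving but unresolved. Section 7.1 names two recruiting sites and Section 3.5 promises support around the clock, so different staff may have to apply it. Two of them could act differently on identical readings, and each could point to the text.

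**Working it through.** No sample size, error rate or event count bears on this point. The check applies each reading to the same values.

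**Inputs**
- Positive ketones: above 0.6 mmol/L (Annex A, return-to-pump rule and Reporting section).
- Persisting hyperglycemia: above 16 mmol/L. Only the lowest band states this; carrying it up to the other bands is an assumption.
- Change test: the bracket in the middle and top bands.
- Paired values below: illustrative, not from the protocol.

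**The two readings**
- Level reading: notify if 2-hour ketones > 0.6 or 2-hour glucose > 16.
- Change reading: notify if 2-hour ketones ≥ starting ketones or 2-hour glucose ≥ starting glucose.

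| Case | Ketones, start to 2 h (mmol/L) | Glucose, start to 2 h (mmol/L) | Level reading | Change reading |
|---|---|---|---|---|
| 1 | 2.8 to 2.6 | 20 to 19 | notify | do not notify |
| 2 | 1.4 to 1.3 | 18 to 14 | notify | do not notify |
| 3 | 1.4 to 1.4 | 18 to 14 | notify | notify |
| 4 | 0.9 to 0.5 | 18 to 14 | do not notify | do not notify |
| 5 | 0.9 to 0.5 | 12 to 12 | do not notify | notify |

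**Main conflict (cases 1 and 2).** Let k0 be the starting ketone value, above 0.6, and k2 the 2-hour value. If k2 ≥ k0, then k2 > 0.6 as well, so the ketone part of the change reading never fires unless the level reading fires too. The converse fails whenever 0.6 < k2 < k0. If glucose has also fallen, nothing else triggers the change reading and the instructions are opposite. From k0 = 1.5 the range is any k2 between 0.6 and 1.5; from k0 = 3.0 it is any k2 between 0.6 and 3.0. Cases 1 and 2 do not depend on the 16 mmol/L assumption, because ketones alone meet the level reading.

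**Reverse conflict (case 5).** Annex A opens by allowing ketone testing on symptoms as well as on glucose above 16 mmol/L, so starting glucose may be 16 or lower. If ketones have dropped to 0.6 or below, while glucose has not decreased and is still not above 16, the bracket triggers a call and the level reading does not. This case does rest on carrying up the 16 mmol/L figure.

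**Where the sentence does not matter.** Starting ketones above 3.0 mmol/L already require immediate physician notification. The practical range for the main conflict is therefore starting values above 0.6 and up to 3.0.

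**The case against.** The strongest defence is that the bracket defines the phrase beside it. On that view *remain positive* simply means not falling for this one rule, and the 0.6 level serves other purposes (return to pump, adverse event documentation). A trend test at two hours is not foreign to the annex either, since the lowest band uses one for ketones. This reading is possible, but the annex does not state it. It would give a word a special meaning in one sentence and the ordinary level meaning shortly afterwards, without notice. Staff cannot tell whether the bracket is a definition, an example or a drafting slip.

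The second defence is that other safeguards apply, and this limits the consequence:
- The nurse is contacted in both upper bands.
- The bands depend on the current reading, so a 2-hour value of 2.6 falls again under the top band.
- Return to pump therapy waits until ketones are below 0.6, whatever the trend.
- Section 3.4 ends the intervention if the situation is unresolved within 6 hours, although that rule is worded for ketones above 1.5 mmol/L.

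A reader might therefore infer too much by concluding that participants with unresolved ketones are left without follow-up; these provisions show otherwise. What they do not settle is whether the physician, as well as the nurse, is told at two hours.

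A reader might also infer that all three bands should use identical wording. The documents do not support that: the lowest band starts at or below 0.6, so *remain positive* cannot apply there, and its rule triggers a different action.

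**Conclusion.** The inconsistency is real and confined to one sentence that appears twice. Its main words and its bracket give opposite instructions when ketones are lower than at the start but still above 0.6 mmol/L and glucose has also fallen. They can conflict in the other direction when ketones have cleared but glucose, never above 16 mmol/L, has not come down.

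The size can be given only as a range of readings. The protocol states no rate of ketone episodes, and a share of the numeric range would say nothing about how many participants are affected.

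A reader might suspect an effect on the trial's results. None follows from this sentence: the endpoints, sample size and primary analysis do not use it, and adverse event documentation of ketones has its own explicit level. The point concerns consistent safety escalation. It should be corrected because the trigger is ambiguous and the correction is small. No view is taken on which criterion is clinically right.

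**What to change.** Reconcile the phrase and its bracket, in both the 0.6 to 1.5 mmol/L band and the band above 1.5 mmol/L, with the use of *positive* in the return-to-pump rule and the Reporting section. State one criterion for ketones and one for glucose, each explicitly as a level, a change from the starting value, or a stated combination. If the bracket is meant as a special definition for this rule, say so and avoid the word *positive* there. The choice belongs to the sponsor's clinicians. The lowest band can keep its own wording.

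The cost is one sentence changed in two places, with matching changes to any participant and nurse instructions that repeat it. Depending on the criterion chosen, there may be a few more calls to the study physician. No new data and no design change are needed.
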